## Abstract

**Background:**

Chronic tinnitus is a common clinical condition with no universally accepted effective treatment option. Increasing evidence suggests that dysfunction within the auditory pathway may contribute to tinnitus pathophysiology, and auditory brainstem response (ABR) has been proposed as a potential objective measure of auditory neurophysiological function. Acupuncture is widely used for tinnitus management; however, the relationship between acupuncture-associated symptom changes and objective electrophysiological alterations remains unclear.

**Objective:**

This study aims to investigate differences in ABR parameters between patients with chronic tinnitus and healthy controls and to explore whether clinical changes following acupuncture intervention are accompanied by alterations in auditory neurophysiological measures.

**Methods:**

This study is designed as a prospective two-part hybrid study protocol consisting of a matched case–control observational component and a longitudinal self-controlled intervention component. A total of 36 patients with bilateral chronic tinnitus and 36 age- and sex-matched healthy controls will be recruited. Both groups of participants will undergo auditory brainstem response (ABR) assessments at baseline and after treatment timepoint; in order to assess test–retest variability, the healthy control group will undergo two ABR measurements. Patients with tinnitus will receive 10 acupuncture treatments over a 4-week period. Clinical outcome measures, including the Tinnitus Handicap Inventory (THI), the Tinnitus Impact Questionnaire (TEQ), and the Tinnitus-Related Visual Analog Scale, will be assessed at baseline, after treatment, and at the 8-week follow-up.

**Expected results:**

This study will characterize baseline differences in ABR parameters between individuals with chronic tinnitus and healthy controls and will examine whether acupuncture-associated improvements in tinnitus symptoms are accompanied by changes in auditory neurophysiological measures. The findings will provide preliminary data regarding the feasibility of ABR as an objective outcome measure for future tinnitus intervention studies.

**Conclusion:**

This protocol describes an exploratory clinical study designed to evaluate clinical and neurophysiological changes associated with acupuncture intervention in chronic tinnitus. The results may contribute to a better understanding of objective electrophysiological assessment in tinnitus research and provide preliminary evidence to support future controlled clinical trials.

**Trial registration:**

https://clinicaltrials.gov/, identifier [NCT07522567]

## Introduction

1

Tinnitus is described as the subjective perception of sound in the absence of an external auditory stimulus. It is frequently characterized as a hissing, buzzing, or ringing sound within the head or ears and can generally be divided into two categories: subjective and objective. Subjective tinnitus, which accounts for the vast majority of cases, is perceived only by the patient and cannot be heard by an examiner. Objective tinnitus, in contrast, is rare and can be auscultated by an examiner, typically arising from somatosensory or vascular causes. Tinnitus can also be categorized as primary (idiopathic, without an identifiable underlying cause) or secondary (associated with a specific identifiable pathology, such as otologic, neurologic, or metabolic disorders) (1). It is a widespread issue that is quite prevalent around the world. According to a 2016 comprehensive systematic review, the reported prevalence of tinnitus varies considerably depending on its definition, ranging from 5.1% to 42.7% globally (2). While transient tinnitus is common, a substantial proportion of individuals experience persistent symptoms. In mainland China, the incidence of tinnitus varied from 4.3% to 51.33%, which was in line with data from around the world. The incidence of tinnitus rose with age, yet no statistically significant sex difference was observed (3). Insomnia, anxiety, depression, and a lower quality of life (QoL) are associated with the severity of tinnitus (4, 5). Furthermore, tinnitus is linked to depression, sleeplessness, cognitive impairment and reduced speech comprehension (6), even in individuals with clinically normal hearing; in fact, 43.8% of tinnitus patients have mental comorbidities (7). Despite its high prevalence and profound impact (8), the underlying pathophysiological mechanisms of tinnitus remain incompletely understood, and no universally effective pharmacological or interventional cures are currently available.

According to the widely adopted clinical classification (9), tinnitus is categorized by duration as acute (<3 months), subacute (3–6 months), and chronic (>6 months). Emerging evidence suggests that chronic tinnitus is not merely a consequence of peripheral cochlear dysfunction but is closely linked to maladaptive neuroplasticity within the central auditory system (10). The prevailing pathophysiological model proposes that tinnitus results from diminished cochlea sensory input, which triggers compensatory homeostatic gain changes along the auditory pathway (11, 12). Moreover, the emotional distress and psychiatric comorbidities commonly associated with tinnitus are increasingly recognized as arising from altered connectivity between auditory and limbic structures, including the amygdala and hippocampus (13). Specifically, even in those with normal audiometric thresholds, disruption to inner hair cell ribbon synapses can decrease afferent input to the auditory nerve, increasing central gain at the brainstem and auditory cortex levels (14, 15). Animal research provides a supporting basis for this process. These studies show that noise exposure can induce cochlear synaptic lesions, which is typically characterized by selective loss of high thresholds auditory nerve fibers. At the same time, an increased spontaneous neural activity and enhanced neural synchrony have also been observed in the thalamus and auditory cortex (16). In general, at least two distinct subtypes of tinnitus are recognized: cochlear tinnitus and central tinnitus. This distinction is supported by the observation that tinnitus is not always abolished following cochlear nerve section (17). Cochlear tinnitus is a kind of tinnitus caused by abnormal cochlear nerve activity. While central tinnitus, in contrast, originates at the cortical level within the central auditory pathways, independent of cochlear nerve activity (12).

The auditory brainstem response (ABR) has become a useful non-invasive method for evaluating the brainstem and auditory nerve pathways’ functional integrity (18). Wave I of ABR originates from the distal portion of the auditory nerve and reflects the summed activity of cochlear afferent fibers, as confirmed by direct intracranial recordings in humans (19), while wave V of ABR is mostly produced in the lateral lemniscus and inferior colliculus, signifying neural processing in the midbrain. A few publications showed that ABR abnormalities are linked to the perception of tinnitus (20). According to Bramhall et al. (21), there is a substantial correlation between a lower ABR wave I amplitude and a greater chance of reporting tinnitus in young individuals with normal audiometric thresholds and normal outer hair cell activity. This association remained after controlling for sex and DPOAE levels. This result supports the theory that the ensuing central gain may strengthen cochlear synapses, which are indicated by a drop in wave I amplitude, hence causing tinnitus (22). Recently, Edvall et al. (23) found that the prolongation of wave V latency in ABR can distinguish between individuals with persistent tinnitus and those who occasionally have tinnitus or no tinnitus. The results show that the transformation from intermittent perception to continuous awareness is related to functional reorganization at the midbrain level. Despite the above progress, there are still no objective biomarkers that can effectively monitor the changes caused by treatment. Most previous findings have been demonstrated at the group level, and the ability of ABR parameters to discriminate tinnitus status or predict individual treatment response remains uncertain. In addition, the exact relationship between electrophysiological changes and clinical symptom characteristics is still not fully clear.

The pathophysiological process of tinnitus is still poorly understood, and the lack of known core causes makes therapy very difficult. For this condition, which affects millions of people, existing treatments including a variety of interventions such as sound therapy, cognitive behavioral therapy, and medication—are effective, but there is no universally effective “gold standard.” Treatment responses vary from person to person, and patients with similar tinnitus characteristics often experience varying degrees of benefit (24). Furthermore, no drugs have been approved by the European Medicines Agency or the U.S. Food and Drug Administration (FDA) to treat tinnitus (25). While carrying out these neurophysiological studies, acupuncture has also become a promising treatment option for chronic tinnitus. As a major treatment modality of traditional Chinese medicine, acupuncture is widely used in East Asia and has gained more and more recognition around the world because of its high patient acceptance and good safety. Systematic reviews and meta-analyses have reported promising but not definitive results for acupuncture in tinnitus (26), and the quality of the existing evidence base remains relatively limited, and methodological flaws have been noted in many of the included studies (27). In order to make up for the above shortcomings, this study pursues two main goals. The first goal is to compare ABR parameters between patients with chronic tinnitus and healthy controls who match their age and sex, so as to explore the relationship between the function of auditory conduction pathways and chronic tinnitus. The second is to measure the ABR parameters and the scores of TEQ (Tinnitus Effects Questionnaire), THI (Tinnitus Handicap Inventory) scales and the Tinnitus-Related Visual Analog Scale. Measurements will be taken before and after 10 acupuncture treatments, as well as at the 8-week follow-up. This allows us to evaluate the therapeutic effect of acupuncture on patients with chronic tinnitus, and explore the possible neurophysiological processes behind it. Notably, emerging preclinical evidence suggests that acupuncture may exert modulatory effects on auditory function at multiple levels of the auditory pathway. For instance, electroacupuncture at the Zhongzhu acupoint (TE3) has been shown to promote neuroplasticity of the central auditory pathway, including the brainstem and auditory cortex, as evidenced by significant changes in auditory brainstem response parameters in both animal models and human studies. These findings provide a neurophysiological rationale for investigating whether acupuncture can modulate ABR parameters in human tinnitus patients (28). Therefore, we propose the following specific hypotheses: Hypothesis 1 (cross-sectional): Patients with chronic tinnitus will show abnormal characteristics on ABR compared with age- and sex-matched healthy controls, reflecting aberrant auditory pathway function. Hypothesis 2 (longitudinal): Following 10 sessions of acupuncture, patients with chronic tinnitus will show significant improvements in THI scores (primary clinical outcome) and concomitant changes in ABR parameters (primary neurophysiological outcome), particularly wave V latency. Hypothesis 3 (association): Changes in ABR parameters from baseline to post-treatment will correlate with changes in clinical outcome measures (THI, TEQ, VAS), supporting a neurophysiological basis for acupuncture’s effects on tinnitus.

## Method

2

### Design overview

2.1

This study adopts a hybrid two-part design comprising a matched case–control observational component and a self-controlled interventional component.

In the first component, patients with chronic tinnitus will be compared with age- and sex-matched healthy controls to identify baseline differences in auditory neurophysiological characteristics, including ABR parameters. In the second component, patients with chronic tinnitus will receive a standardized acupuncture intervention and will be followed longitudinally to evaluate changes in subjective tinnitus severity and auditory neurophysiological function. Healthy controls will also undergo two ABR assessment over a comparable time interval to estimate test–retest variability and distinguish treatment-associated changes from normal measurement variability.

There is no sham acupuncture control group in this study. We acknowledge that placebo effects, expectation-related responses, and other non-specific effects associated with acupuncture cannot be completely excluded and may influence the interpretation of treatment-associated changes. To minimize the placebo effect, a strict assessor-blinded design will be adopted. The ABR waveforms will be anonymized and coded before interpretation, with audiologists blinded to both group allocation and time points. Clinical scale interviewers will be blinded to time point, and data analysts will work on a fully coded dataset until the final analysis is locked.

In addition, although the following measures will not reduce the placebo effect, we will take further steps to ensure the overall scientific rigor and interpretability of the study results. Baseline characteristics of all participants will be compared to verify the comparability between the tinnitus and healthy control groups. During recruitment, participants will be provided with standardized information regarding the study procedures, potential benefits, possible adverse reactions, and the sensory experiences associated with acupuncture. The information will be presented in a balanced manner to ensure adequate understanding of the intervention without emphasizing potential treatment outcomes. Furthermore, subjective questionnaire data will be evaluated alongside objective ABR measures to provide complementary information regarding clinical changes and associated neurophysiological alterations. The Standard Protocol Items: Recommendations for Interventional Trials (SPIRIT) guidelines will be followed in the development of the protocol (29). Zhejiang Chinese Medical University’s Third Affiliated Hospital will host the study. A total of 72 participants will be included in this study, including 36 patients with chronic tinnitus and 36 healthy controls who matched the patient in age and sex. Healthy controls will be individually matched with tinnitus participants according to sex and age within ±3 years. In addition to demographic matching, we will also compare PTA and audiogram characteristics between the two groups at baseline, as well as before and after treatment within each group. If there are significant intergroup differences in audiogram characteristics, these specific frequencies will be included as covariates in the statistical model used to compare auditory brainstem response (ABR) parameters between groups. The treatment plan includes 10 sessions of acupuncture, which can be completed within 4 weeks and carried out three times a week (usually 2 days apart between each treatment). There are three time points used to evaluate tinnitus-related clinical outcomes and auditory brainstem response (ABR) parameters, namely the baseline period (before the start of treatment), the end of the course (within 1 week after the tenth treatment), and the 8th week after the completion of treatment as follow-up point. The Institutional Ethical Review Board (IRB) of the Third Affiliated Hospital of Zhejiang Chinese Medical University has granted ethical permission for the trial (ZSLL-KY-2025-032-01), which will be conducted in accordance with the Declaration of Helsinki. The Ethics Committee will be notified right away of any amendments to the study design. NCT07522567 is the identification code for this trial’s registration in the Clinical Trials Registry. Table 1 displays the study’s SPIRIT list, while Figure 1 displays the flow diagram.

**Table 1 tab1:** SPIRIT schedule of enrollment, interventions, and assessments.

	Study period							
	Enrolment	Allocation	Treatment period				Post-treatment	Follow-up
TIMEPOINT (week)	Week −1(T0)	Week 0	W1	W2	W3	W4	W5 (T1)	W13 (T2: 8-week FU)
Enrolment								
Eligibility screen	X							
Informed consent	X							
Demographic/medical history	X							
Allocation		X						
Interventions								
Acupuncture (10 sessions, 3×/week)			X	X	X	X		
Assessments								
ABR parameters	X						X	
Pure-Tone Threshold testing	X							
Tympanometry & Acoustic reflex testing	X							
DPOAEs	X							
Otoscopic examination	X							
THI	X						X	X
TEQ	X						X	X
Loudness/Annoyance VAS	X						X	X
Adverse events			X	X	X	X	X	

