#### Inclusion criteria

2.3.1

1) Diagnosis of bilateral chronic subjective tinnitus (including primary and secondary tinnitus, as well as cochlear and central cases), with a duration of at least 6 months, and a score of at least 16 on the Chinese version of the THI scale (mild) (30);2) Pure-tone average hearing threshold (PTA) < 20 dB HL in both ears, with no individual frequency exceeding 30 dB HL (31);3) Normal tympanometric findings, acoustic reflection test findings, sotoscopic examination findings and normal Distortion product otoacoustic emissions (DPOAEs);4) Aged between 18 and 60 years, inclusive, any sex;5) Both tympanic membranes are intact and the external auditory canal is clear;6) Sufficient expressive and comprehensive language skills, adequate cognitive function, and the capacity to collaborate with the study’s experimental procedures;7) Signing the informed consent form and not taking part in any other interventional clinical trials at this time.

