### Outcome measures

2.7

The outcomes of this study were designed to evaluate both the clinical efficacy and neurophysiological changes associated with acupuncture treatment in patients with chronic tinnitus. Considering the different characteristics of subjective symptom assessment and electrophysiological evaluation, clinical and neurophysiological outcomes will be analyzed separately.

The assessment schedule is summarized in Table 1. Patient-reported outcomes, including tinnitus severity and related functional impairment, will be assessed at baseline (T0), after completion of acupuncture treatment (T1), and at the 8-week (after the beginning of acupuncture treatment) follow-up visit (T2). Auditory brainstem response (ABR) measurements will be performed in both the healthy control group and the tinnitus patient group at baseline (T0) and after treatment completion (T1), as the primary purpose of the electrophysiological assessment is to evaluate changes in auditory pathway function during the course of treatment. ABR testing will not be conducted at the follow-up visit, as the primary purpose of the follow-up assessment is to evaluate the durability of subjective tinnitus improvement.

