
### Limitations and future directions

3.1

This study has a number of limitations. Its sample size is comparatively modest because it is a single-center study. Therefore, the results may not be fully extended to a wider range of people with tinnitus. Another limitation is that the intervention group did not include a tinnitus control group receiving sham treatment, making it impossible to compare the effects of true acupuncture and sham acupuncture on patients with tinnitus. This is particularly worthy of attention, because the 2024 VA/DOD guidelines found insufficient evidence of acupuncture, and thus emphasized the need to carry out good controlled trials. While the self-controlled design allows each patient to serve as their own control and reduces between-subject variability, it cannot fully distinguish specific acupuncture effects from placebo effects, regression to the mean, or non-specific treatment effects. Although the inclusion of a healthy control group with repeated ABR measurements helps quantify normal test–retest variability, it does not replace a parallel sham-controlled arm. Therefore, our findings should be interpreted as preliminary and hypothesis-generating. Future adequately powered, sham-controlled randomized trials are needed to definitively establish the efficacy of acupuncture for chronic tinnitus. Third, the ABR protocol in this study uses broadband click stimuli rather than frequency-specific tone bursts. While this choice ensures clinical standardization and comparability with previous literature, it may reduce the sensitivity to detect frequency-specific cochlear synaptopathic changes that have been suggested to underlie some forms of tinnitus (51). Future studies incorporating multiple frequency-specific stimuli (e.g., 1, 2, and 4 kHz tone bursts) would provide a more comprehensive assessment of the relationship between acupuncture, ABR parameters, and tinnitus pathophysiology. Fourth, this study employs an assessor-blinded design rather than a double-blind design. Due to the nature of the acupuncture intervention, neither patients nor acupuncturists can be blinded to treatment allocation, which may introduce performance bias and expectation effects. To mitigate this, we have implemented several measures which have been motioned in the Design overview section. Nonetheless, we acknowledge that the lack of patient blinding remains a limitation. Fifth, treatment adherence is currently assessed primarily by session attendance, which does not fully capture treatment fidelity. To strengthen this aspect, all acupuncturists will follow a detailed Standard Operating Procedure (SOP) manual, needle manipulation parameters (angle, frequency, and duration) will be recorded for each session, and the De Qi sensation will be assessed using the C-MASS scale after each session. These additional measures will allow us to characterize the consistency of treatment delivery beyond simple attendance records. In addition, although ABR measurement is valuable for evaluating brainstem function, it cannot capture changes in the cortical level, which may also affect the perception of tinnitus. Lastly, this study did not set up a long-term follow-up beyond the treatment period, so it is impossible to evaluate whether the observed effect is persistent. And the 8-week follow-up assessment was conducted by telephone, which may introduce recall bias and reduce the accuracy of symptom evaluation compared with face-to-face assessment.

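### Interviewers cannot be blinded to time point at a telephone follow-up, and telephone mode is confounded with time in every THI comparison that involves T2

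*Protocol article*

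**What the plan says.** Section 2.1 (Design overview) acknowledges that there is no sham group and continues: "To minimize the placebo effect, a strict assessor-blinded design will be adopted". It then lists the elements of that design: coded ABR waveforms read by audiologists blinded to group and time point, analysts working on coded data, and, for the patient-reported scales, "Clinical scale interviewers will be blinded to time point". The next paragraph introduces further measures by conceding that those will not reduce the placebo effect, which implies that the blinding just described does.

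Other sections bear on this:

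- Table 1 has one pre-treatment THI, in the Week −1 (T0) enrolment column that also holds the row "Eligibility screen". Section 2.3.1 requires a THI of at least 16 for entry.
- Section 2.7 schedules ABR at T0 and T1 and states that "ABR testing will not be conducted at the follow-up visit".
- Section 3.1 (Limitations) says "And the 8-week follow-up assessment was conducted by telephone", and names recall bias and lower accuracy "compared with face-to-face assessment" as possible results.
- Section 2.7.1.1 defines the primary clinical outcome as THI change from baseline to both post-treatment and follow-up. Section 2.8 analyses it by one-way repeated-measures ANOVA over T0, T1 and T2, in patients only.
- Section 3.1 also says that patients cannot be blinded, and points back to the Design overview measures as mitigation.

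**The concern.** The plan claims a safeguard for its primary clinical outcome that its own follow-up procedure rules out. Three separate problems follow.

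First, whoever makes the telephone call knows that it is the follow-up, so the unqualified statement about time point fails at T2.

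Second, if T2 is the only telephone assessment, any systematic difference between telephone and in-person answers enters the time effect. With no parallel patient group assessed on the same schedule, later analysis cannot separate the two.

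Third, THI, TEQ and VAS are the patient's own reports. Hiding the visit from the interviewer can limit interviewer influence, but it leaves untouched the expectation of a patient who knows that acupuncture was given.

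In a study without a sham arm, readers will give real weight to the stated blinding when they judge the THI result.

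**Working it through.** No figure in the plan is at issue, so the check is mainly a comparison of sections, followed by an illustrative calculation.

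**Can the interviewer be blinded at each time point?**

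| Time point | What the plan describes | Blinded to time point? |
|---|---|---|
| T0 | Same column as eligibility screening and consent; THI is an entry criterion; ABR done | Doubtful, unless a separate interviewer unaware of the visit is used; none is described |
| T1 | ABR done, so apparently on site | Not settled by the text |
| T2 | Telephone; no ABR | No: the call identifies the visit |

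**Which THI comparisons are confounded with mode?** In-person assessment at T0 and T1 is inferred from the ABR schedule and from the contrast drawn in section 3.1; it is not stated outright. On that reading:

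- T0–T1: same mode, so not confounded with mode.
- T0–T2 and T1–T2: mode changes for every patient exactly when time changes, so confounding is complete.
- Omnibus test over three time points: includes T2, so affected.

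**How much could a mode shift matter?** The inputs from the plan are the planned THI change of 12.07 points and its SD of 23.28 (section 2.9), 36 patients, two-sided alpha 0.05, and 20% attrition, which leaves 36 × 0.80 = 28.8, about 29. The mode shift b is an assumption: 2 to 5 points, constant across patients, of unknown direction.

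Standard error of the mean change: SE = SD/√n.

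- n = 36: 23.28/6 = 3.88
- n = 29: 23.28/√29 = 4.32

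With no true T0–T2 change, the paired t statistic follows a noncentral t distribution with n − 1 degrees of freedom and noncentrality b/SE. The two-sided rejection rate is the probability that it falls beyond either critical value.

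| Assumed shift b | Share of 12.07 | b/SE, n = 36 | Rejection, n = 36 | Rejection, n = 29 |
|---|---|---|---|---|
| 0 | 0% | 0 | 5% | 5% |
| 2 | 17% | 0.52 | 7.9% | 7.3% |
| 3 | 25% | 0.77 | 11.7% | 10.3% |
| 5 | 41% | 1.29 | 24.1% | 20.1% |

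The rates are the same for a shift in either direction. If telephone answers run lower, the T0–T2 improvement looks larger; if they run higher, real benefit is partly hidden. With a true change of 12.07 and a 5-point shift, the expected observed change would be 17.07 or 7.07.

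Three approximations apply. The SD is the plan's value for change after treatment and stands in for the T0–T2 SD, which is not given. The calculation uses a paired t-test for one contrast, not the three-time-point ANOVA. The shift has no source in the documents.

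**The case against.** The strongest reply is that much of this is already disclosed. Section 3.1 admits that the telephone follow-up may bring recall bias and lower accuracy, that patients are not blinded, and that the findings are preliminary and hypothesis-generating. Section 2.1 says that placebo effects cannot be completely excluded. All of that is in the text. But nowhere does the article reconcile the telephone call with the blinding statement or say that mode changes together with time, and it cites the Design overview measures as mitigation. The contradiction remains.

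Several stronger readings are tempting, and the documents do not support them:

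- *All three time points are unblinded.* A reader might infer that the interviewer must know T0 because THI decides entry, and then identify T1 by elimination. The article does not say who administers the THI. A separate interviewer given coded visits is conceivable and could be described in the full protocol. T0 blinding is doubtful, not disproved, and the step to T1 depends on it.
- *The whole primary THI outcome is confounded with mode.* T0–T1 apparently shares one mode, and the THI sample size rests on the change after treatment.
- *A VAS cannot be given by telephone.* Section 2.7.2.1 specifies 0–10 scores, and such a rating can be given orally.
- *The error rate is known to be inflated.* The 2 to 5 points are an assumption.

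It may also be said that interviewer knowledge adds little to an uncontrolled pre–post comparison already open to placebo response and regression to the mean. That limits the practical harm, but it also shows why assessor blinding should not be presented as the answer to the placebo effect.

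**Conclusion.** The point holds in a limited form. The blinding statement is wrong for T2 and doubtful for T0. Telephone mode is completely confounded with time in T0–T2, T1–T2 and the omnibus THI test, provided that T0 and T1 are on site, as the plan implies. The claim that assessor blinding minimises the placebo effect does not hold for self-reported scores from unblinded patients.

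The size of any mode effect is unknown. The range of about 8% to 24% against a nominal 5% shows only what an assumed shift of 2 to 5 points would do to one contrast with 36 patients.

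This should be corrected, but it does not undermine the study: T0–T1 remains usable as far as mode is concerned, and the study is described as exploratory.

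**What to change.** In section 2.1, restrict the blinding statement to ABR reading and data analysis, and delete the claim that assessor blinding minimises the placebo effect. Adjust the reference back to those measures in section 3.1. This costs wording only.

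For the scales, take one of two routes:

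1. Collect THI, TEQ and VAS in the same mode at T0, T1 and T2, for example on the same self-completed paper or online form. This removes the mode change and any dependence on an interviewer. The cost is a mailed or online form at T2, and perhaps a reminder call to keep up the return rate.
2. If the telephone follow-up stays, name T0–T1 as the primary THI contrast, report T2 separately, and state that it is confounded with mode. This costs no extra fieldwork, but the durability result then carries less weight.
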